## **8.2. General considerations**

The analyses will be performed based on the intention- to-treat principle. Baseline variables by treatment groups will be characterized in a summary table. Between-group differences at baseline will be inspected and judged according to clinical relevance. The assessment of compliance with the intervention and safety/tolerability will be summarized for both groups. Adverse events, if any, will be reported by treatment group.

## **8.3 Analysis of the primary outcome**

For the primary outcome data analysis, we will adopt the generalized linear model (GLM) to investigate the change in systolic blood pressure (SBP) at 40 minutes versus at 0 minutes between intervention and control groups. Specifically, we will treat the difference between the average of the triplicate SBP measurements at 0 minutes and 40 minutes at each infusion as the outcomes in the GLM, adjusting for covariates such as intervention, age and sex. The generalized estimating equation (GEE) technique is proposed to estimate the regression coefficients, and the corresponding variances are estimated by the sandwich estimators. GEE will be used to account for the clustering (non-independence) of the data attributed to the longitudinal and repeated measures design of this study. A Gaussian regression with an identity link for continuous outcomes will be used to estimate mean differences between treatment groups, fitted with robust error estimation and an ar1 working correlation structure. We will use Inverse-probability

weighting (IPW) to account for missing data and augmentation (AUG) for imbalance in  
covariates between treatment groups for doubly robust GEE estimation.

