### **4.4 Randomization Process**

Patients who successfully complete the screening assessments will be randomized into the study. Eligible patients will be 1:1 randomized to the music-intervention (intervention, n=15) or usual care (control, n=15) groups. Participants will be randomized by an independent third party affiliated with McGill University using a computer-generated randomized sequence. The randomization sequence code will stored securely for the duration of the trial. The only theoretical exception for the code to be broken will be any serious adverse event and need for subsequent participant withdrawal.

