### **7.1.2 Blood pressure and hemodynamic function**

Prior to every infusion and at 15, 30 and 40 minutes (end of infusion), baseline vital signs, including heart rate, respiratory rate, oxygen saturation, and blood pressure will be measured. Blood pressure change measurement will be assessed by a validated and calibrated Welch Allyn Blood Pressure Device according to Hypertension Canada Guidelines and recommended technique for automated office blood pressure. The patient will be semi-reclined (approximately 45 degrees) on the treatment bed or medical lounger, the back supported, the arm bare and supported, legs uncrossed, not talking or moving before or during the measurement, using a cuff size appropriate for the arm (i.e bladder width close to 40% of the arm circumference and length cover 80-100% of the arm circumference), the middle of the cuff at heart level, with the lower edge of the cuff 3 cm above the elbow crease. The initial measurement will be taken after 10 minutes of quiet rest, as described above. No change in bed/recliner position will be permitted during or between ketamine infusions. This technique will be used to measure the change in systolic blood pressure (SBP) at 40 minutes versus at 0 minutes between intervention and control groups. Specifically, we will treat the difference between the average of the triplicate SBP measurements at 0 minutes (measurement taken at 1 minute interval as recommended) and the

508 average of the triplicate SBP measurements at 40 minutes (measurement taken at 1 minute  
509 interval), at each infusion.

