## 8. Statistical analysis

### 8.1 Sample size calculation

This study is a pilot trial. There is currently limited data to justify the sample size, given the innovative nature of studying music on hemodynamic tolerance during sub-anesthetic ketamine infusions. Furthermore, performing a priori power analyses with a within-subject factor is complicated and difficult to perform accurately without a prior study to justify correlations between levels and sphericity assumptions. This pilot RCT will thus provide the necessary and adequate data to plan a subsequent confirmatory RCT.

A preliminary power analysis was done to estimate the number of patients required for this study and computed a priori using the software G\*Power 3.1, University Düsseldorf, Germany. The sample size calculation was based on the results of Mok et al. who studied the impact of music on hemodynamic functioning in preoperative patients, given the similar within-between study design and procedure. They found pre-post differences of systolic blood pressure of  $-3,5 \pm 14.5$  mmHg in the music group and no changes ( $+0,1 \pm 10,3$  mmHg) in the control group. A two-sided 0.05

level of significance and a sample size of 28 patients (14 patients per group), each providing six pre-post datapoints, provided 80% statistical power to significantly demonstrate this difference in systolic blood pressure, assuming sphericity of 1 and correlations among measures of 0.5. To accommodate for a 10% attrition rate (given low attrition rate in ketamine trials for depression, we will recruit a total of 30 patients (G\*power 3.1, ANOVA Repeated measures, within between interaction), a feasible recruitment rate at the current clinical capacities over 12-18 months.

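### The primary analysis of SBP change names no baseline SBP as a covariate, in the GEE or in the augmentation step, leaving the estimate sensitive to chance imbalance between arms of 15

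*Supplement*

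**What the plan says.** Section 7.1.2 defines the primary variable at each infusion as the "difference between the average of the triplicate SBP measurements at 0 minutes" and the corresponding triplicate average at 40 minutes. Section 8.3 uses that difference as the outcome in a Gaussian, identity-link GEE with AR1 working correlation and sandwich variances, "adjusting for covariates such as intervention, age and sex". It adds inverse-probability weighting for missing data and an augmentation step for covariate imbalance between arms, without listing the covariates of either. Section 8.2 says that baseline differences will be looked at and weighed by clinical relevance; it gives no rule linking this to the model.

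The data for a baseline covariate are already collected. Sections 6 and 7.1.2 provide for triplicate SBP after ten minutes' rest before every infusion, and the table in 7.3 shows blood pressure at screening. Section 4.4 randomises after screening ("Eligible patients will be 1:1 randomized", 15 per arm) and mentions no stratification.

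**The concern.** Subtracting the 0-minute value fixes the slope of 40-minute on 0-minute SBP at 1. If the true slope is lower, as regression to the mean usually makes it, the arm that starts higher by chance will tend to show a smaller rise whether or not music works. With 15 patients per arm, no stratification described and deliberately permissive recruitment (section 3), a baseline difference of several mmHg is an ordinary event.

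Two things are at stake. The first is how to read the one estimate this trial will produce, which section 8.1 says will be used to plan a confirmatory trial. The second is that the covariate list is open. If baseline SBP may or may not enter, the choice can be made after the data are seen, and the two choices can give noticeably different answers.

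**Working it through.** **Inputs from section 8.1.** Source-study changes are -3.5 (SD 14.5) with music and +0.1 (SD 10.3) without. The planned difference is therefore 3.6 mmHg. The pooled change SD is sqrt((14.5² + 10.3²)/2) = 12.58, so d = 3.6/12.58 = 0.286 and f = d/2 = 0.143. The stated design is "A two-sided 0.05" level, "a sample size of 28 patients (14 patients per group"), six datapoints each, correlation 0.5; then "we will recruit a total of 30 patients".

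**The plan's own figure.** Section 8.1 says this "provided 80% statistical power". For the named test (within-between interaction), the noncentrality is f²·N·m/(1-ρ) = 0.143²·28·6/0.5 = 6.88 on 5 and 130 degrees of freedom. That gives 47% power, so the 80% is not reproduced from the stated inputs. This is a separate matter, noted here only because it shows how little precision there is to spare.

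**Inputs not in the documents.** The SD of 0-minute SBP (SD0) is assumed to be 12, 15 or 18 mmHg. With equal variances at 0 and 40 minutes, the slope equals the correlation r, and the change SD is SD0·sqrt(2(1-r)). Holding the change SD at 12.58 fixes r = 1 - 12.58²/(2·SD0²).

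**Shift from chance imbalance, single occasion.** The standard error of the baseline difference is SD0·sqrt(2/15). The shift per standard error is (1-r) times that. Percentages use unrounded values.

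| SD0 | r | SE of baseline difference | Shift per 1 SE | Share of 3.6 |
|---|---|---|---|---|
| 12 | 0.45 | 4.38 | 2.41 | 67% |
| 15 | 0.65 | 5.48 | 1.93 | 53% |
| 18 | 0.76 | 6.57 | 1.60 | 45% |

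**Averaging six infusions.** If 60% of the variance in 0-minute SBP lies between patients (assumed), the SD of a six-infusion mean is sqrt(0.6 + 0.4/6) = 0.816 of the single-occasion SD. The shifts fall by about 18%, to 1.96, 1.57 and 1.31 mmHg (55%, 44% and 36% of 3.6).

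**Simulation check.** With 15 per arm, six infusions and the same 60% share, three settings lie near the plan's change SD. The gap is between unadjusted and adjusted estimates.

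| SD0 | r | Mean absolute gap (mmHg) | 95th percentile | Trials with gap above 1.8 mmHg |
|---|---|---|---|---|
| 12.6 | 0.5 | 1.49 | 4.11 | 32% |
| 15 | 0.7 | 1.07 | 3.10 | 19% |
| 18 | 0.8 | 0.89 | 2.69 | 14% |

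**Precision.** The ratio of adjusted to change-score variance is (1-r²)/(2(1-r)) = (1+r)/2. At r = 0.5 this is 0.75 (SE down 13%); at r = 0.8 it is 0.90 (SE down 5%). That is the full gain, with the 0-minute SBP of the same infusions as covariate. One infusion-1 value per patient recovers the fraction 0.6 + 0.4/6 = 0.667 of the variance reduction under the same assumed share. The SE then falls by 1 - sqrt(1 - 0.667·0.25) = 9% at r = 0.5, or 1 - sqrt(1 - 0.667·0.10) = 3% at r = 0.8.

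**Power.** For a constant 3.6 mmHg difference, the SD of a patient's six-infusion mean change at correlation 0.5 is 12.58·sqrt((1 + 5·0.5)/6) = 9.61. With 15 per arm, power is 17.5% (normal approximation), rising to 21.9% (r = 0.5) or 19.0% (r = 0.8) with full adjustment.

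**The case against.** The strongest reply is that the plan does not rule adjustment out. The covariate list in 8.3 is worded as examples, and the augmentation step is aimed at covariate imbalance. This stands: the fault is that baseline SBP is unspecified, and a reader who infers that the plan excludes it goes further than the text. It does not rescue the plan, because an unnamed covariate protects nothing until someone chooses it.

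A reader might also infer that the result is confounded. It is not. Allocation is randomised, the change-score estimate is unbiased over randomisations, and its standard error already includes chance imbalance. What remains is dependence on the imbalance in this trial, and lost precision.

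Nor do the documents support saying that imbalance moves the estimate by most of the planned effect. They give no baseline SD or correlation. A larger shift such as 3.3 mmHg pairs SD 18 with slope 0.5, which implies a change SD of 18, well above the plan's 12.6. If SBP varies more at 40 minutes than at 0, the slope could be nearer 1 and the shift smaller.

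Finally, the precision gain is modest and would not by itself alter what a pilot can conclude. That also stands; the case rests on the change being almost free. Section 8.2 describes inspecting a baseline table and does not say that covariates will be chosen from it.

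**Conclusion.** The point holds as a specification gap with a moderate consequence. The primary model is a change-score model in which baseline SBP is pre-specified neither in the GEE nor in the augmentation. Under the stated assumptions (SD 12 to 18 mmHg, equal variances, change SD 12.6), a one-standard-error imbalance on one occasion moves the estimate by about 2.4 to 1.6 mmHg against a planned 3.6. After averaging six infusions this becomes about 2.0 to 1.3 mmHg. The loss of precision is small to moderate. The direction of the argument needs only a slope below 1; the size depends on quantities the documents do not report.

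**What to change.** In section 8.3, replace the open-ended covariate wording with a closed list: intervention, age, sex and one pre-treatment SBP per patient. Name the same list for the augmentation, and state that inspection of the baseline table under 8.2 will not change the primary model.

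Choose the baseline in advance. Screening SBP precedes randomisation. The 0-minute SBP at infusion 1 is measured in the same way as the outcome, but section 6.1 lets music-arm patients hear playlist excerpts that day before treatment starts.

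Keep a model with each infusion's own 0-minute SBP as a sensitivity analysis only. At infusions 2 to 6 that value follows earlier sessions with or without music, so adjusting for it could remove part of the effect. Infusion number and site are optional.

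The cost is wording and one more parameter with 30 clusters. No new data are needed. A single pre-treatment value gives up part of the full precision gain, which is the price of a covariate that earlier music sessions cannot have affected.

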### 3. Study Design

This is a prospective, two-center, single-blinded, pragmatic randomized controlled trial with a parallel two-arm design to be performed in Montreal, Canada. Patients with TRD will be recruited. After completing all screening / evaluations and baseline procedures, patients will be randomized in a 1:1 ratio to receive a curated music intervention (described below), which will consist of 60 minutes of music initiated at the beginning of each infusion (intervention group) or usual care (no music; control group) during a course of six sub-anesthetic ketamine infusions. Patients who meet all inclusion criteria and none of the exclusion criteria will be entered into the study. Recruitment criteria will be intentionally permissive in order to generate results of high external validity by including clinically representative patients who may often be excluded from clinical trials. Thirty (n=30) patients are planned for enrollment in this pilot RCT. Hemodynamic evaluations will be taken at each infusion and, for the primary outcome of blood pressure, an average of the triplicate blood pressure measures by a calibrated Welch Allyn Blood Pressure Device at 0 minutes and at 40 minutes (end of infusion) will be used. Secondary outcomes will be measured at baseline and at each treatment session, as well as at 8-week follow-up. The total duration of patient participation is expected to be eight weeks including four weeks of active treatment. The total duration of the study is expected to be two years.

The study will be a two-center study performed in the Montreal area; patients will be prospectively recruited by solicitation of clinicians and by screening of ongoing referrals at the ketamine services of two academic hospitals (the Douglas Mental Health University Institute and the Jewish General Hospital) by research assistants not actively involved in their care. The

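### Primary GEE analysis relies on sandwich variances with only 30 patients and names no small-sample correction or reference distribution; the nominal 5% test rejects about 8–9% of the time

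*Supplement*

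**What the plan says.** Section 8.3 takes the difference between the averaged triplicate systolic readings at 0 and 40 minutes as the outcome at each infusion. It fits a Gaussian identity-link GEE with intervention, age and sex given as examples of covariates. On variance it says that "the corresponding variances are estimated by the sandwich estimators" and that the model is "fitted with robust error estimation and an ar1 working correlation structure". It adds inverse-probability weighting for missing data and augmentation for covariate imbalance.

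Section 3 gives the number of independent units: "Thirty (n=30) patients are planned for enrollment in this pilot RCT". Section 4.4 allocates 15 to each arm. The significance level appears only in Section 8.1: "A two-sided 0.05" "level of significance and a sample size of 28 patients (14 patients per group), each" giving six pre-post values.

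Sections 8.2 to 8.5 name no bias-corrected variance, t or F reference, permutation test or bootstrap.

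**The concern.** The sandwich variance is justified when the number of independent clusters is large. Here the clusters are patients. Six infusions per patient add rows but no clusters, and arm, age and sex vary only between patients. With about 30 clusters and four patient-level parameters (intercept, arm, age, sex), the fitted residuals are too small and the standard sandwich variance is biased downward. A normal reference adds to the error because it ignores the uncertainty in the variance estimate.

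The single primary p-value and its confidence interval are at stake. Both look more certain than they are, and the intervals may be carried into the confirmatory trial that Section 8.1 says this pilot will inform.

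**Working it through.** **The plan's own figure.** Section 8.1 gives no error rate for the GEE, only 28 patients for 80% power. With a difference of 3.6 mmHg and a pooled SD of √[(14.5² + 10.3²)/2] = 12.58, d = 3.6/12.58 = 0.286 and f = d/2 = 0.143. The named G*Power test (within-between interaction, six measures, correlation 0.5, sphericity 1) then gives 47% power at N = 28. The 80% figure was not reproduced. That is a separate matter; only the counts 28 and 30 are used below.

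**Inputs.** From the documents: N = 30 (Section 3) or 28 (Section 8.1), equal arms, six values per patient, correlation 0.5 (Section 8.1), AR(1) working correlation, and arm, age and sex (Section 8.3). Assumed: standard sandwich, complete data, no true effect, true correlation exchangeable or AR(1) at 0.3 to 0.7.

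**Approximate size by hand.** With p = 4 patient-level parameters, average leverage is p/N and the standard error shrinks by about √(1 − p/N).
- N = 30: √(1 − 4/30) = 0.931. The effective critical value is 1.960 × 0.931 = 1.825, and P(|t₂₆| > 1.825) ≈ 8.0%.
- N = 28: √(1 − 4/28) = 0.926. The effective critical value is 1.960 × 0.926 = 1.815, and P(|t₂₄| > 1.815) ≈ 8.2%.

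**Simulation under the null**, true correlation 0.5, 40,000 trials per row. With complete data and patient-level covariates, the GEE reduces to a regression on weighted patient means.

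| Two-sided rejection at nominal 5% | N = 30 | N = 28 |
|---|---|---|
| Standard sandwich, normal reference | 8.2% | 8.6% |
| Standard sandwich, t on N − 4 df | 6.9% | 7.1% |
| Standard sandwich, no covariates, normal | 6.9% | 7.0% |
| Augmented estimator, normal | 9.0% | 9.5% |
| Augmented estimator, t | 7.7% | 8.0% |
| Kauermann-Carroll, t on N − 4 df | 5.2% | 5.2% |
| Mancl-DeRouen, normal | 4.6% | 4.6% |

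The Monte Carlo standard error is about √(0.082 × 0.918/40,000) = 0.14 percentage points. The augmented rows use arm-specific outcome models in age and sex; Section 8.3 does not say which models are intended.

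**Sensitivity.** Full GEE runs (4,000 per scenario) over the correlation structures gave about 8.0–9.6% at N = 30 and 8.5–9.4% at N = 28 with the standard sandwich and normal reference. With unequal arm SDs of 14.5 and 10.3 the rates were 7.8% (N = 30) and 9.1% (N = 28). At N = 200 the rate was 5.7%, so the excess comes from the small number of patients.

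**Standard errors and coverage.** The standard sandwich SE was 0.89–0.94 of the true SD of the estimate, that is 6–11% too small. Coverage of nominal 95% intervals is 100 − 8.2 = 91.8% (N = 30) or 100 − 8.6 = 91.4% (N = 28). For the augmented estimator it is 91.0% and 90.5%.

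**Direction.** Under the null about half of the rejections favour each arm. False findings that music lowers systolic pressure are therefore about 8.2/2 = 4.1% to 9.0/2 = 4.5%, against a nominal 5/2 = 2.5%.

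**The case against.** The plan does not exclude a correction. Bias-corrected estimators are also sandwich estimators, and the source cited for the doubly robust GEE, which is not available here, may carry its own variance procedure. A reader might infer that the sponsor has chosen an uncorrected sandwich with a Wald z-test. The documents do not say so; both are inferred from silence, and the 8–9% figure depends on both. This stands, so the point is one of missing specification. It does not remove the concern: the link, working correlation, weighting and augmentation are all stated, the variance is not qualified, and every uncorrected variant tried exceeded 5%.

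Two other strong readings also fail. One is that a false claim of benefit occurs 9% of the time against 5%. That compares two-sided rejections with a claim in one direction. The other is that the rate exceeds 10%. That needs extra patient-level covariates which Section 8.3 does not name, although its covariate list is open-ended.

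The simulations had complete data and no estimated weights, so they do not cover the whole planned procedure. This stands as a limit on the size of the effect.

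Finally, this is a pilot and the point estimate is not in question. That lowers the severity. It does not make the error rate irrelevant, since Section 2.1 states a hypothesis of a significant reduction and Section 8.1 sets a 0.05 level with 80% power.

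**Conclusion.** The concern holds as an omission with a measurable consequence. Section 8.3, followed with the standard sandwich and a normal reference, gives a primary test that rejects about 8–9% of the time at a nominal two-sided 5%. With t alone the rate is about 7–7.5%, and for the augmented estimator simulated it is about 9–9.5%. Standard errors are roughly 10% too small.

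These figures assume 28 to 30 patients, adjustment for age and sex, and complete data. Without covariates the excess is smaller, about 7%. The contribution of estimated inverse-probability weights is unknown. For a pilot this should be fixed, but it does not undermine the design.

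**What to change.** In Section 8.3, pre-specify one correction and one reference distribution. Suggested text: *Standard errors use the Kauermann-Carroll corrected sandwich, with tests and 95% confidence intervals on a t distribution with N minus p degrees of freedom, where p is the number of patient-level parameters.* In simulation this gave about 5.2–5.8%. Mancl-DeRouen also controls the error, but it behaves differently, so the choice should not be left open. Close the covariate list as well, since p depends on it.

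For the weighted and augmented fit, where this correction was not tested, name either a permutation test that follows the actual allocation scheme or a patient-level bootstrap. Weights and outcome models should be re-estimated in each replicate. Neither option was simulated here. A linear mixed model with Kenward-Roger degrees of freedom is an optional sensitivity analysis.

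The cost is one or two sentences, a software option and wider intervals. At N = 28 and correlation 0.5 the widening is about (1.003/0.923) × (2.064/1.960) = 1.14, or 14%, from the ratio of corrected to standard SE and of the t₂₄ to normal critical values. Sample size and data collection do not change.
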